## Abstract

**Background:**

Antipsychotics are essential in the acute treatment of and maintenance therapy for schizophrenia, but medication adherence and long-term treatment continuity are needed to maximize their effectiveness. Each antipsychotic has various side effects, which may affect adherence. Some patients with schizophrenia are reluctant to take asenapine because of its unique oral-related side effects, such as the bitter taste caused by sublingual administration. Our previous basic research found that D-sorbitol lowered the bitterness parameters of the taste sensors. However, whether D-sorbitol has the same effect in patients remains unclear. Therefore, using a D-sorbitol solution, we aim to evaluate changes in the bitterness of asenapine among patients with schizophrenia.

**Methods:**

In this single-blind, placebo-controlled, crossover trial, we plan to recruit 20 adult patients with schizophrenia spectrum disorder who take sublingual asenapine tablets. The participants will be divided into two groups (*n* = 10 each). Each group will be given a D-sorbitol or placebo solution on the first day for rinsing before taking the sublingual asenapine tablets. After a 1-day interval, the participants will rinse their mouths again with a different liquid. Questionnaires regarding changes in taste and the willingness to continue asenapine will be conducted before the start of the study and after each rinse. The primary and secondary end points will be a taste evaluation of bitterness, and the willingness to continue asenapine, respectively. Differences in questionnaire scores between the D-sorbitol and placebo solutions will be calculated and analyzed using a McNemar test.

**Discussion:**

This study aims to determine the efficacy of D-sorbitol in masking the bitter taste of asenapine. To our knowledge, it is the first intervention study using D-sorbitol for bitter taste of asenapine in patients with schizophrenia. Evidence of the efficacy of D-sorbitol could result in D-sorbitol pretreatment being an easy and inexpensive means of improving adherence to asenapine.

**Trial registration:**

This study was registered in the Japan Registry of Clinical Trials jRCTs041210019, on May 14, 2021. Ethics approval was obtained from the Nagoya University Clinical Research Review Board.

## Background

Antipsychotics are essential in the acute treatment of and maintenance therapy for schizophrenia. Maintenance of antipsychotic drugs not only prevents relapses and rehospitalizations, but also benefits patients in terms of quality of life [1]. All antipsychotics reduce overall symptoms more than do placebos, but they do not show clinically significant differences among drugs in terms of efficacy, except for clozapine [2]. Therefore, medication adherence and long-term treatment continuity are needed to maximize their effectiveness. In addition, the side effects of antipsychotics, especially metabolic side effects and those related to extrapyramidal symptoms, affect medication adherence [3].

Each antipsychotic has a unique safety profile that may affect adherence. Asenapine is the only sublingual antipsychotic approved (in 2009) by the United States Food and Drug Administration (FDA). A network meta-analysis of 32 oral antipsychotics reported that asenapine is effective against the positive, negative, and depressive symptoms associated with schizophrenia [2]. Several lines of evidence show that asenapine has minimal effect on metabolic side effects such as weight gain, glucose intolerance, and prolactin elevation [2, 4]. In addition, asenapine has been shown to be associated with a lower incidence of extrapyramidal side effects compared with other newer second-generation antipsychotics [5]. Although asenapine is associated with a lower risk of adverse events affecting medication adherence, it has characteristic side effects that may affect its tolerability.

Asenapine has unique oral-related side effects, such as the bitter taste caused by sublingual administration, so some patients with schizophrenia are reluctant to take it. For example, approximately 10% of patients reported experiencing oral hypoesthesia [6], and 6.5% of patients stopped taking their medication because of the bitter taste [7]. Asenapine is in a sublingual form because of its high first-pass effect. For this reason, patients should avoid eating or drinking for several minutes after administration to prevent a decrease in bioavailability [8]. Therefore, patients may need to tolerate the bitter taste of asenapine for a few minutes, which may affect adherence and compliance with the dosing procedure.

Reducing the bitter taste of pharmaceutical preparations is widely accepted as a way of improving patient adherence and compliance to a therapeutic drug regimen [9]. Dealing with the bitter taste of asenapine is critical for improving adherence. Our previous basic research showed that D-sorbitol lowered the bitterness parameters of the taste sensors [10]. D-Sorbitol is widely used in oral care products and has been approved as a pharmaceutical product, which makes it easy to use in a practical way. However, whether D-sorbitol has the same effect in patients remains unclear. Therefore, we decided to conduct a crossover study utilizing D-sorbitol as the primary endpoint to evaluate changes in the taste of asenapine in patients with schizophrenia. As a secondary endpoint, we will also conduct a survey on the willingness to continue asenapine.

## Methods

### Study design

The purpose of this single-blind, placebo-controlled, crossover study is to evaluate the efficacy of D-sorbitol in masking the bitter taste of sublingual asenapine tablets. D-Sorbitol oral solution 75% (KOWA, Aichi, Japan) will be used as the test solution in this study. The dosing period will be 1 day each in study periods ① and ②. Taste evaluations will be performed at home for outpatients and during hospitalization for inpatients, with a 1-day test interval to eliminate the carryover effect of D-sorbitol. Patients will be given an oral rinse with D-sorbitol or a placebo solution before taking the sublingual asenapine tablets. Then, after a 1-day interval, the patients will rinse their mouths again with a different liquid than that used on day 1. A questionnaire survey regarding taste evaluations and the intention to continue asenapine with the intervention will be conducted on the participants before the start of the study and after each rinse.

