### Experimental schedule

The experimental schedule is shown in Table 1 and Fig. 1. The study will have two groups. Group A will receive D-sorbitol first (test period ① using D-sorbitol and test period ② using placebo solution), and Group B will receive the placebo solution first (test period ① using placebo solution and test period ② using D-sorbitol). There will be a 1-day interval between study periods ① and ②. The study will be conducted in the ward for inpatients and at home for outpatients at the same time of day as the administration of the sublingual asenapine tablets. The participants will provide the following information: disease onset category, duration of illness from the first onset, DSM-5 specific terms, total Positive and Negative Syndrome Scale score at enrollment, sublingual asenapine tablet starting date, asenapine dosage, concomitant medications, comorbidities, smoking history, height, and weight. Before the study, the participants will complete a multiple-choice questionnaire regarding the side effects and duration of getting used to asenapine. Also, after the study is completed, a questionnaire regarding the efficacy of the intervention will be administered.

**Table 1 Tab1:** Experimental schedule

	Experimental schedule				
	Baseline	Experimental period			Discontinuation
Day	Day 0	*Day 1*	*Day 2*	*Day 3*	
Participant background	○				
PANSS	○				
Height, weight	○				
Pre-questionnaire	○				
*Oral rinse with* *D**-sorbitol or placebo*		○		○	
*Post-implementation questionnaire*		○		○	
*Adverse events*					○

*PANSS* Positive and Negative Syndrome Scale

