### Primary outcome

The primary end point is the taste evaluation of bitterness, which addresses post-implementation question 2. The participants will self-assess on a 7-point scale regarding the use of D-sorbitol and the reduction of the bitter taste.

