### Secondary outcome

The secondary end point will be the willingness to continue asenapine, subjectively self-rated on a 5-point scale, which addresses post-implementation question 3. The use of mouthwash before taking asenapine is expected to reduce its bitterness. There is expected to be a need to evaluate whether the reduction of bitterness affects adherence to asenapine.

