### Statistical analysis

The primary endpoint was evaluated on a 7-point Likert scale, with 1 to 3 points defined as improvement and 4 to 7 points as non-improvement. The secondary endpoint was evaluated on a 5-point Likert scale, with 1 to 2 points defined as improvement and 3 to 5 points as non-improvement. The difference in population proportions for improved/non-improved binary data will be analyzed using a McNemar test. Participants with missing data will be excluded from the analysis, and no interim analyses will be performed.

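### Taste and willingness to continue are said to be surveyed before the study, but the Day 0 form rates neither, and the post-rinse items name no fixed reference intake

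*Protocol article*

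**What the plan says.** Two places describe a survey of both outcomes before the study.

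- Abstract, Methods: "Questionnaires regarding changes in taste and the willingness to continue asenapine will be conducted before the start of the study and after each rinse".
- Study design: "A questionnaire survey regarding taste evaluations and the intention to continue asenapine with the intervention will be conducted on the participants before the start". The same sentence adds a repeat following both rinses.

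Two others describe what is collected on Day 0.

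- Experimental schedule: before the study, "the participants will complete a multiple-choice questionnaire regarding the side effects and duration of getting used to asenapine". Table 1 puts only this pre-questionnaire on Day 0, beside background data, PANSS, height and weight.
- Questionnaire survey content prints its three items: time to get used to the tablets, time to get used to their taste, and a checklist of adverse events.

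The endpoints come from the post-rinse form alone. Primary outcome: "The primary end point is the taste evaluation of bitterness, which addresses post-implementation question 2". Secondary outcome: "subjectively self-rated on a 5-point scale, which addresses post-implementation question 3". Under Statistical analysis the primary item is dichotomised "with 1 to 3 points defined as improvement and 4 to 7 points as non-improvement", and "The difference in population proportions for improved/non-improved binary data will be analyzed using a McNemar test".

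**The concern.** The statements in the Abstract and Study design do not match the printed form. This is not condensation by the journal, because the article lists the items.

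The mismatch matters because the primary item is a change rating with an open reference. Post-question 2 asks how bitter the tablet was against what the patient felt in the past, and names no intake. In post-question 3, options 2 to 4 compare with an unspecified earlier state, while options 1 and 5 are absolute. On Day 1 the only possible reference is asenapine without a study rinse. On Day 3 it could also be the Day 1 rinse. The Randomization and blinding section makes that comparison plausible: patients know they are evaluating two solutions for bitterness and can tell them apart by sweetness.

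A second consequence is independent of the reference. Entry requires more than 2 weeks on asenapine but no bitterness. Option 1 of post-question 2 describes an absolute level, almost none, yet counts as improved. A patient who never found the tablet very bitter can choose it after both rinses. That pair is concordant and contributes nothing to the McNemar test, and no Day 0 bitterness level is recorded to identify the patient.

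**Working it through.** **Text check**

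| Topic | Abstract and Study design | Experimental schedule and Questionnaire survey content |
|---|---|---|
| Taste before the study | surveyed | time to get used to the taste only; no bitterness level |
| Willingness before the study | surveyed | no item |
| Reference for post-question 2 | not stated | past bitterness, no intake named |
| Reference for post-question 3 | not stated | an earlier state, no intake named, in 3 of 5 options |

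**The plan's own figure.** The Participants section gives 18 analysed (9 per group) with 10% dropout: 18 / (1 − 0.10) = 20, which reproduces the recruitment target. The 18 itself cannot be checked, because no discordant proportions are given. The illustration below therefore uses assumed improvement rates that are not in the document.

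**Illustration of a moving reference.** Take 9 patients per sequence and improvement against the usual tablet with probability 0.75 on D-sorbitol and 0.20 on water, independently within patient.

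- Improved on D-sorbitol only: 0.75 × 0.80 = 0.60, so 18 × 0.60 = 10.8 pairs.
- Improved on water only: 0.25 × 0.20 = 0.05, so 18 × 0.05 = 0.9 pairs.
- Improved on both: 0.75 × 0.20 = 0.15, so 18 × 0.15 = 2.7 pairs, 1.35 in each group.

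Now let every patient judge period 2 against the Day 1 rinse. A patient improved on both rates the second rinse as unchanged. In Group A (D-sorbitol first) the water rating becomes non-improved, which adds 1.35 pairs for D-sorbitol. In Group B (water first) the D-sorbitol rating becomes non-improved, which adds 1.35 pairs for water. The discordant pairs move from 10.8 versus 0.9 to 12.15 versus 2.25.

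Full enumeration of the uncorrected McNemar test, rejecting when (b − c)² / (b + c) ≥ 3.84 (b and c being the two discordant counts), by share of patients who re-anchor:

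| Assumed rates, D-sorbitol / water | none | 25% | 50% | all |
|---|---|---|---|---|
| 0.75 / 0.20, power | 0.916 | 0.883 | 0.854 | 0.807 |
| 0.70 / 0.20, power | 0.850 | 0.814 | 0.781 | 0.728 |
| 0.80 / 0.30, power | 0.850 | 0.790 | 0.741 | 0.682 |
| 0.40 / 0.40, type I error | 0.043 | 0.042 | 0.041 | 0.038 |

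With an uneven 11 to 7 split and equal rates of 0.40, type I error stays between 0.041 and 0.043.

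The power loss depends on the model. It assumes that a patient improved on both rinses sees no difference between them. If patients rate on an underlying continuous scale, so that they can still find D-sorbitol better than water, the loss is smaller and can be close to nil.

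**The case against.** The strongest reply has four parts.

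1. **The early sentences may be loose summaries.** Change in taste, or intention to continue with the intervention, cannot be rated before any rinse. This is plausible, but the text then needs correcting.
2. **The reference is natural.** These patients have taken asenapine for more than 2 weeks, so past bitterness most readily means their usual experience. Table 1 has no rinse on Day 2, so if usual dosing continues, an unrinsed tablet falls between the two ratings. The forms are also in Japanese, and the wording patients see is not shown. All this makes re-anchoring less likely. It does not fix the reference, and the 1-day interval is meant for carryover of D-sorbitol, not for this.
3. **A within-patient comparison needs no baseline.** True for the McNemar test itself. A baseline is needed to describe who had bitterness to reduce. The item on time to get used to the taste helps only in part, because it gives no level.
4. **Re-anchoring is an inference.** It is. The document neither states it nor rules it out.

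A reader might go further and infer a bias in favour of D-sorbitol, since in Group A re-anchoring pushes the water rating towards no change or stronger. That follows one sequence only; Group B shifts the other way, and Fig. 1 plans 10 patients in each. Nor does it size the problem to note that 6 discordant pairs to 0 give an exact p of 2 × 0.5⁶ = 0.031, as that is a general property of the test.

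**Conclusion.** The contradiction over Day 0 stands on the text alone. The open reference in the sole primary item is a real weakness of measurement, but the documents do not support a claim of false-positive risk or of systematic advantage to D-sorbitol.

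The supported consequences are an ambiguous period 2 rating, a possible loss of power, and no recorded Day 0 bitterness level to show which patients had bitterness to reduce. The power loss ranges from little or none to 0.92 falling to 0.81 at 0.75 / 0.20, or 0.85 to 0.68 at 0.80 / 0.30, both with every patient re-anchoring. These figures rest on assumed rates, independence within patient and 9 patients per sequence; how many patients would re-anchor is unknown. The correction is worth making because it is cheap and the ambiguity cannot be repaired once the forms are filled in.

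**What to change.** - Word post-questions 2 and 3 identically on Day 1 and Day 3 against one stated reference, for example *compared with your usual tablet without any rinse, before this study*.
- Add to the Day 0 form a bitterness rating of the usual tablet and the ease-of-continuing item. This makes the statements in the Abstract and Study design true, and lets patients without baseline bitterness be described.
- If the Day 0 items are not added, correct those two statements to match the printed pre-questionnaire.

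The cost is two extra items, reworded post-rinse questions and one minor amendment, with no change to design, sample size or primary test. Repeating a 0–10 bitterness rating after each rinse, with a supporting paired analysis, is optional.

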### Participants

Patients attending or hospitalized at the Department of Psychiatry, Nagoya University Hospital, Nagoya, Japan, will be included in the study. The sample size was set as 20 by the following statistical calculation. Using the 7-point Likert scale, we defined 1 to 3 points as improved and 4 to 7 points as non-improved. The McNemar test was used to estimate the sample size for the improved/non-improved binary data. McNemar’s test was used to determine the number of cases required to obtain a significant difference (significance level: 5% two-sided) with more than 90% power in the crossover study. As a result, the number of cases to be analyzed was nine for each group (18 cases in total), assuming a dropout rate of 10%. To reach the target sample size, we will recruit through advertisements at Nagoya University Hospital.

The inclusion criteria are as follows: 1. Adult patients with schizophrenia or psychotic features based on the Diagnostic and Statistical Manual of Mental Disorders, 5th edition (DSM-5), regardless of gender; 2. Patients using sublingual asenapine tablets for more than 2 weeks; and 3. Patients who can provide written informed consent. The exclusion criteria are: 1. Patients with physical diseases or symptoms requiring medical treatment; 2. Pregnant and lactating women; 3. Patients with a history of convulsions; 4. Patients with a substance use disorder; 5. Patients with a taste disorder; 6. Patients with an olfactory disorder; 7. Patients who cannot understand the questionnaire protocol; and 8. Other patients whose inclusion in the study is deemed inappropriate by the attending physician. We will interview participants to determine if they meet these exclusion criteria. The reason for excluding olfactory disorder is that an associations between olfactory and bitter taste receptors has been suggested, and olfactory disorder may also affect the evaluation of taste [11]. The discontinuation criteria are: 1. If the research participant requests discontinuation; and 2. If the attending physician determines that there will be a clear disadvantage in the participant’s disease.

### Randomization and blinding

The primary investigator or coinvestigators will enroll and assign the participants to the investigations. Two groups will be randomly assigned using the envelope method. D-Sorbitol and placebo will be administered in clear containers, as they are visually indistinguishable. The participants can distinguish between the two liquids based on their level of sweetness. We just informed the patients that we would ask them to evaluate the effect of the two different solutions on bitterness but did not indicate which flavor was the placebo. Even if they can distinguish between the liquids, blindness is expected to be maintained. Only the participants will be blinded.

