### Study drug

Participants will receive D-sorbitol as the active drug and distilled water as the placebo. Participants will rinse with 25 mL of the study drug immediately before taking the sublingual asenapine tablet. Both D-sorbitol and distilled water will be kept clear and colorless to maintain blinding. During the study period, patients will be instructed to rinse their mouths by themselves at home or in the hospital ward. Afterwards, the patients will answer a multiple-choice questionnaire, which will be collected later.

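### Blinding is expected to hold although participants, the only blinded party and the raters of both endpoints, can tell the two rinses apart by taste

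*Protocol article*

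**What the plan says.** Study design declares the blinding level and the aim: "The purpose of this single-blind, placebo-controlled, crossover study is to evaluate the efficacy of D-sorbitol in masking the bitter taste". It also names the active rinse: "D-Sorbitol oral solution 75% (KOWA, Aichi, Japan) will be used as the test solution in this study". Study drug gives the comparator: "Participants will receive D-sorbitol as the active drug and distilled water as the placebo". The masking feature described there is visual: "Both D-sorbitol and distilled water will be kept clear and colorless to maintain blinding".

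Randomization and blinding then makes three statements close together:

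- On taste: "The participants can distinguish between the two liquids based on their level of sweetness".
- On the consequence: "Even if they can distinguish between the liquids, blindness is expected to be maintained".
- On who is masked: "Only the participants will be blinded".

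The support offered is that participants were told they would judge how two different solutions affect bitterness, and that the team "did not indicate which flavor was the placebo".

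Under Primary outcome and Secondary outcome, both endpoints are self-ratings by the participant (7-point bitterness change, 5-point ease of continuing). Statistical analysis dichotomises both and uses a McNemar test. The limitations paragraph of the Discussion does not mention expectation or blinding.

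**The concern.** The protocol grants that the one masked party can perceive the difference between the arms, then treats masking as intact. Matching color cannot conceal a taste difference in liquids held in the mouth, and in a crossover each participant tastes both.

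Blinding in this trial is meant to protect the rating. Nobody other than the participant rates either endpoint, so no second, masked assessment stands behind the result. If participants favor the sweet rinse because they take it to be the one meant to help, that preference enters the McNemar table exactly as true masking would. The label of single-blind and placebo-controlled would then promise a separation of the two that the design does not secure.

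**Working it through.** **Setting the statements side by side**

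1. The liquids differ in taste: 75% D-sorbitol against distilled water (Study design; Study drug).
2. The difference is perceptible, which the protocol states as fact (Randomization and blinding).
3. Each participant meets both liquids, on Day 1 and Day 3 (Table 1).
4. Each participant knows that the question is the effect on bitterness (Randomization and blinding).
5. The participant supplies both endpoints (Primary outcome; Secondary outcome).

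Points 1 to 4 give participants what they need to form a view of which rinse is under test. The withheld label removes confirmation of that view but does not prevent it. Point 5 carries the view into the data. The category boundary is also close: on the 7-point item, 4 is no change and 3 is a slight reduction, so a shift of one step turns non-improved into improved.

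**Illustration of scale**

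Inputs from the protocol: 18 analysed participants and a two-sided 5% McNemar test (Participants; Statistical analysis). The step from 18 to 20 enrolled is consistent: 18/(1 − 0.10) = 20. The protocol gives no discordant proportions, so the following inputs are assumed:

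- No true masking, and background discordance of 5% each way, leaving 90% concordant, all taken as improved on neither rinse.
- Expectation turns the rating of the sweet rinse to improved in a share x of participants. Concordant pairs then become improved on D-sorbitol only; pairs improved on water only become improved on both.

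With p10 = improved on D-sorbitol only and p01 = improved on water only:

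p10 = 0.05 + 0.90x, p01 = 0.05(1 − x)

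The probability of significance is the sum of trinomial(18; p10, p01, 1 − p10 − p01) probabilities over all tables with exact two-sided McNemar p ≤ 0.05. For example, 6 versus 0 discordant pairs gives p = 2 × 0.5⁶ = 0.031 and rejects; 5 versus 0 gives 2 × 0.5⁵ = 0.0625 and does not.

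| x | p10 | p01 | Significant |
|---|---|---|---|
| 0 | 0.050 | 0.0500 | below 0.1% |
| 0.05 | 0.095 | 0.0475 | 0.3% |
| 0.10 | 0.140 | 0.0450 | 1.7% |
| 0.20 | 0.230 | 0.0400 | 13% |
| 0.30 | 0.320 | 0.0350 | 37% |
| 0.40 | 0.410 | 0.0300 | 63% |

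**Sensitivity**

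- Setting p10 = 0.05 + x and p01 = 0.05 gives 15%, 38% and 62% at x = 0.20, 0.30 and 0.40.
- If x is instead the whole of p10 (p10 = x, p01 = 0.05), the same three values give 7%, 26% and 51%.
- The protocol does not say which form of McNemar test will be used. With the uncorrected asymptotic test, rejecting when (b − c)²/(b + c) ≥ 3.84 for discordant counts b and c, p10 = 0.05 + x and p01 = 0.05 give 35%, 56% and 74%.

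**The case against.** The strongest reply is that telling two liquids apart is not the same as knowing which is the placebo. The protocol draws that distinction deliberately, and it stands in part. A reader might infer that participants are in fact unmasked, but the text admits only that the liquids are distinguishable. It does not say whether participants even know that one liquid is a placebo. What the distinction does not support is an expectation that blinding holds, since the route to inference stays open.

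Second, a taste agent may be impossible to match: an equally sweet control might itself mask bitterness. This is fair, and no better comparator is proposed here. It excuses the design but not the sentence about blinding. No change of wording will restore participant masking.

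Third, a reader might infer that leaving staff unblinded is a further error. The documents do not support that. The trial is openly single-blind, participants rinse and answer a multiple-choice form themselves, and no investigator scores either endpoint. The text does not say who collects the forms.

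Fourth, the illustration rests on chosen rates. That is correct: with the exact test, effects of 5% or 10% stay below the nominal 5%, and the larger figures need large expectation effects.

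**Conclusion.** The point holds. The protocol claims a property that its own neighboring sentence undercuts, and both endpoints depend on that property. With the trial as described, a positive result would show that a D-sorbitol rinse was rated better than a water rinse. It would not show how much of the difference is masking and how much is expectation.

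The size cannot be derived from the documents. Under the stated assumptions, the chance of significance without any true masking runs from about 0.3% at a 5% expectation effect to 63% at 40%. It would be wrong to read any one of these as the trial's false-positive rate, or to conclude that a positive result would be spurious.

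This should be fixed but does not block the trial: the distinguishability is disclosed, and what needs correcting is the inference drawn from it and the scope of the conclusion.

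**What to change.** 1. **Wording.** In Randomization and blinding, replace the sentence that expects blinding to be maintained with a statement that the liquids are matched in appearance only and that participants may infer the allocation. Add expectation bias to the limitations in the Discussion. Limit the conclusion to D-sorbitol rinse versus water rinse, including any expectation effect. The cost is a more modest claim.

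2. **One guess item.** Ask which rinse the participant believes they received, preferably after the Day 1 rinse and before the tablet, so that the answer is less mixed up with any real change in bitterness. Otherwise place it in the planned end-of-study questionnaire, accepting that someone whose bitterness fell will tend to name that liquid as the active one. Report it descriptively by sequence, without a subgroup test: about 18 people are too few to split by guess. The cost is one extra item, which may itself draw attention to the allocation. An early item must be very short, because the protocol has the tablet follow the rinse immediately.

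3. **Optional.** The liquids look alike, so bottles could be coded to keep staff unaware of the order. This is good practice rather than a correction.

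None of these changes alters the sample size, the rinse days or the endpoints.
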